# Digital wound monitoring with artificial intelligence to prioritise surgical wounds in cardiac surgery patients for priority or standard review: protocol for a randomised feasibility trial (WISDOM)

**DOI:** 10.1136/bmjopen-2024-086486

**Published:** 2024-09-17

**Keywords:** WOUND MANAGEMENT, Artificial Intelligence, Telemedicine, Clinical Trial, eHealth, Infection control

## Abstract

**Introduction:**

Digital surgical wound monitoring for patients at home is becoming an increasingly common method of wound follow-up. This regular monitoring improves patient outcomes by detecting wound complications early and enabling treatment to start before complications worsen. However, reviewing the digital data creates a new and additional workload for staff. The aim of this study is to assess a surgical wound monitoring platform that uses artificial intelligence to assist clinicians to review patients’ wound images by prioritising concerning images for urgent review. This will manage staff time more effectively.

**Methods and analysis:**

This is a feasibility study for a new artificial intelligence module with 120 cardiac surgery patients at two centres serving a range of patient ethnicities and urban, rural and coastal locations. Each patient will be randomly allocated using a 1:1 ratio with mixed block sizes to receive the platform with the new detection and prioritising module (for up to 30 days after surgery) plus standard postoperative wound care or standard postoperative wound care only. Assessment is through surveys, interviews, phone calls and platform review at 30 days and through medical notes review and patient phone calls at 60 days. Outcomes will assess safety, acceptability, feasibility and health economic endpoints. The decision to proceed to a definitive trial will be based on prespecified progression criteria.

**Ethics and dissemination:**

Permission to conduct the study was granted by the North of Scotland Research Ethics Committee 1 (24/NS0005) and the MHRA (CI/2024/0004/GB). The results of this Wound Imaging Software Digital platfOrM (WISDOM) study will be reported in peer-reviewed open-access journals and shared with participants and stakeholders.

**Trial registration numbers:**

ISRCTN16900119 and NCT06475703.

STRENGTHS AND LIMITATIONS OF THIS STUDYMixed methods, including qualitative and quantitative data, will provide in-depth information on satisfaction and acceptability.The study will evaluate the feasibility, acceptability and safety of the intervention and provide data to inform an adequately powered subsequent randomised trial.The economic investigation comprises an initial scoping exercise and an economic evaluation on completion of the clinical study.A study is limited to testing feasibility and is not powered to test the effectiveness of the intervention.

## Introduction

 Surgical site infections (SSIs) are among the most common healthcare-associated infections globally, with the WHO reporting one-third of all patients in lower-income and middle-income countries developing a wound infection after surgery.^1^ These problematic and infected wounds are distressing for patients and can result in increased readmissions and further surgery.^2 3^ There are also additional costs to healthcare providers and to patients.^4 5^

Most wound problems, present after patients have been discharged from the hospital^6^ and this figure continues to increase through initiatives such as enhanced recovery programmes which promote early patient discharge.^7^ It is important to identify and treat problematic wounds quickly as delays in treating a wound can allow problems to worsen making them harder and more expensive to treat.^8^ Therefore, identifying wound problems and infections after discharge is becoming increasingly important.

Digital remote surgical wound monitoring offers a solution to monitoring wounds in patients’ own homes.^9^ With digital monitoring, patients upload images of their wounds and some information using their smartphone in response to weekly preprogrammed text messages which are then reviewed by specialist nurses.^10^

Evaluations of digital wound monitoring including a systematic review find wound infections are detected earlier, readmissions and further surgeries are reduced, the burden on the hospital services is reduced, carbon emissions are reduced and patient satisfaction is high.^9^,^11^ Digital surgical wound monitoring is being used in several countries including the USA, the UK and Brazil, and its uptake is increasing. For example, at one group of hospitals in the UK, over 7000 surgical patients have submitted over 50 000 images for review over the past 3 years.^10^ This creates a new and additional workload for staff.

Artificial intelligence (AI) has been used to support the assessment of chronic wounds,^12^ but as yet, there has been limited use of AI in the monitoring of surgical wounds or the diagnosis or infections. One study was identified that used machine learning to predict patients that were likely to develop an SSI following orthopaedic surgery and another study in Spain used AI to identify patients with SSIs by reviewing patients’ clinical records.^13 14^

The aim of this feasibility study is to assess a surgical wound monitoring platform that uses AI to assist clinicians to review patients’ wounds by prioritising images for urgent review. This will manage staff time more effectively and expedite treatment.

The objectives are to obtain safety, feasibility and acceptability outcomes data plus obtain data for economic modelling.

## Methods and analysis

### Study design

This is a two-centre, unblinded parallel-group randomised feasibility study with safety, acceptability and health economic outcomes comparing the AI module with standard care. 120 adult patients having coronary artery bypass grafting (CABG) surgery will be randomised into two groups. Both patient groups will receive standard wound care following surgery, with the intervention group also receiving a digital wound monitoring platform with an AI module. Data are collected at baseline, and 30 days and 60 days after surgery through surveys, interviews, case note review, platform review and phone calls. The protocol was developed using the Standard Protocol Items: Recommendations for Interventional Trials guidelines.^15^

### Patient and public involvement

To determine patient and public views on using digital surgical wound images, we commissioned a national survey through the patient association which received around 400 completed responses.^16^ Our evaluation of the monitoring platform at five cardiac centres with 137 patients helped identify outcome measures, and 30 bedside pilots helped with platform development.^17 18^ This patient engagement led to changes to the platform relating to, for example, text message content, camera function and an email option. Our trial protocol was discussed with a Cardiovascular Lay Advisory Group. We have patient and public involvement (PPI) and equality, diversity and inclusion (EDI) representatives as coapplicants for the study and people with lived experience are represented on our Research Steering Group. This paper is coauthored with PPI and EDI representatives.

### Eligibility criteria

#### Settings

Two cardiac centres have been selected for recruitment: one in the north of England and one in the south. One city-based centre provides a wide range of patient ethnicities and performs around 1000 cardiac procedures each year. The second centre has a wide geographical spread including patients from rural and coastal locations and performs around 300 cardiac procedures each year.

#### Participants

Patients are eligible to take part if they are 18 years old, or over, having CABG surgery. Patients having first or redo CABG surgeries with or without adjunct cardiac procedures such as valve replacement, or chest reopening during the same admission as index surgery are eligible. Patients remain eligible despite the presence of a wound complication or infection, providing it is not a pre-existing SSI. Patients without a smartphone are eligible if they are willing to use a smartphone or internet provided by the study or if their next of kin or carer has a smartphone. Patients with a physical disability such as visual impairment will be eligible if their next of kin or carer is able to provide assistance.

Patients will not be eligible to take part if they require a ventricular assist device or extracorporeal membrane oxygenation, are ventilated or unconscious.

Patients who do not speak English and do not have a carer who can translate for them will not be able to participate in this feasibility study because of the need for free-text communication between patients and Isla. We are interested to know if/how age, sex, location (eg, rural/urban), socioeconomic status, ethnicity, English-speaking/non-English-speaking and carer involvement influence patient engagement with digital wound monitoring. However, we acknowledge that, due to the limited number of patients in this study and the restriction requiring English speakers (or patients with English speaking carers) any findings will be tentative and will require confirmation in a later definitive study.

#### Sample size

This is a feasibility study, and therefore, sample size calculations cannot be calculated as there are no current data which can be used as the basis of the calculations. The feasibility outcomes for this study are all binary outcomes, for which the widest CIs will occur with a proportion of 0.5 (or 50%), therefore, calculating a sample size for the CI based on 50% gives a ‘worst case’ estimate.

Recruiting 60 patients for each treatment group into the trial (ie, a total of 120 patients) will enable us to estimate the recruitment and drop-out rates with a 95% CI of within ±10% even if the rates were 50% for these two feasibility outcomes. (The 95% CI for a sample size of 120 patients and 60 successes, ie, 50% of patients recruited, or 50% of patients completing the study, is 41% to 59%). If the adherence to treatment rate is 50%, the adherence rate and 95% CI could be estimated to within ±13%. (The 95% CI for 30 adherent patients out of 60, as this is only relevant for patients in the intervention group, is 37%–63%). The sample size estimations were calculated using STATA V.18 with command ‘cii proportions’.

In addition, national data show a wound problem rate of 21% (our data shows 15%) with a cardiac wound infection rate of 8%.^19 20^ A sample size of 120 patients should provide around nine patients in each group with a wound problem of which 4–5 patients should have a wound infection. This is sufficient to inform feasibility, safety and acceptability data.

With a potential sample size of 1300 patients, we plan to recruit 120 patients over 10 months, a recruitment rate of around 11%. This should be achievable as a randomised trial using patients’ smartphones to monitor surgical wounds had a 69% recruitment rate.^9^

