### Data analysis

Descriptive statistics will be presented to summarise the distribution of baseline variables across each of the randomisation groups. Continuous variables (age, height, weight, body mass index, quality of life) will be reported with means and 95% CI, if shown to be normally distributed, using a combined skewness and kurtosis test, otherwise will be reported with medians and IQR. The categorical and ordinal variables (eg, sex, ethnicity, disability, diabetes, smoker status, skin tone, socioeconomic status, surgical procedure, length of stay, carer status, partner status, owned smartphone, resources given to patient such as ipad, mobile, pay as you go and internet) will be reported with frequencies and percentages.

Safety outcomes, such as the quality of images received and assessed by clinicians at 30 days, will be reported using frequencies and percentages. Qualitative data from the interviews will be analysed using thematic analysis.

For acceptability outcomes, variables that are continuous will be reported with means and CIs, if shown to be normally distributed, using a normality plot, otherwise, they will be reported with medians and IQRs. Categorical variables (eg, sex, ethnicity) will be reported with frequencies and percentages.

Feasibility outcomes relating to adherence will be reported as the number and percentage of adherent patients in the intervention group. To be adherent a patient needs to submit one photo with a completed questionnaire within the 30-day period. This will be compared with the progression criteria defined below (table 1). The definitive study will proceed (or not) based on these outcomes. The number and percentage of eligible patients recruited for the study will be reported. The feasibility outcomes will be reported with 95% CI.

**Table 1 T1:** Progression criteria

Criteria	Do not proceed	Proceed with changes	Proceed
Recruitment	<10% of eligible patients consent	Between 10% and <25% of eligible patients consent	At least 25% of eligible patients consent
Adherence with the module	<40% of intervention patients submit one or more images	Between 40% and <80% of intervention patients submit one or more images	At least 80% of intervention patients submit one or more images
Loss to follow-up	<10% of intervention patients complete the study	Between 10% and <60% of intervention patients complete the study	At least 60% of intervention patients complete the study

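### The 41%–59% interval given for the recruitment rate uses the 120 recruited patients as its denominator, so it belongs to a different ratio; the error is conservative and needs only a wording correction

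*Protocol article*

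**What the plan says.** The Sample size section of the protocol article offers no power calculation. It justifies the size, 60 per group and 120 in all, by precision, taking a proportion of 50% as the worst case. The claim is that this number "will enable us to estimate the recruitment and drop-out rates with a 95% CI of within ±10" percentage points, and it is meant to hold at that worst case. The support is a single interval that serves two outcomes. For recruitment it reads: "The 95% CI for a sample size of 120 patients and 60 successes, ie, 50% of patients recruited". The same sentence then turns to completion and gives the limits: "or 50% of patients completing the study, is 41% to 59" per cent. A separate interval for adherence uses 30 of the 60 intervention patients and is given as 37% to 63%. The software is named: "The sample size estimations were calculated using STATA V.18 with command ‘cii proportions".

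Three other statements fix what the recruitment rate is:

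- Data analysis: "The number and percentage of eligible patients recruited for the study will be reported".
- Table 1, lowest recruitment band: "<10% of eligible patients consent". The other cut-off, 25%, has the same denominator.
- Sample size, last paragraph: "With a potential sample size of 1300 patients, we plan to recruit 120 patients over 10 months, a recruitment rate of around 11"%.

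**The concern.** One ratio, 60/120, is made to stand for two different quantities. For completion it works: 120 are randomised and 60 of them complete. For recruitment it does not. Sixty recruited out of 120 would be a trial of 60, half the planned size. The last paragraph of the same section treats 120 as the numerator, over a pool of potential patients.

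Precision is the main numerical argument for 120 patients, and recruitment is one of the three outcomes it is argued for. Recruitment is also a progression criterion. A reader who takes 41% to 59% at face value learns nothing about how precisely the recruitment rate will be known, near the 10% and 25% cut-offs or anywhere else.

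**Working it through.** **Inputs.** From Sample size: 120 recruited, 60 per group; 95% two-sided interval; 60/120 and 30/60 as worked examples; potential pool 1300; 10 months; about 11%. From Data analysis and Table 1: denominator is eligible patients; cut-offs 10% and 25%. From Settings: about 1000 and about 300 cardiac procedures a year at the two centres.

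**Method.** Exact (Clopper-Pearson) interval for x successes in n, assumed to be what the named command gives by default:

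- lower limit = 2.5% point of Beta(x, n − x + 1)
- upper limit = 97.5% point of Beta(x + 1, n − x)

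**Step 1: reproduce the plan's figures.**

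- 60/120: 40.7% to 59.3%, half-width (59.26 − 40.74)/2 = 9.3 points. Rounds to the stated 41% to 59%. The Wald interval (41.05% to 58.95%) and Wilson interval (41.2% to 58.8%) round the same way, so the choice of method is not the issue.
- 30/60: 36.8% to 63.2%, half-width 13.2 points. Rounds to the stated 37% to 63%.

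The arithmetic is right; the ratio is wrong for recruitment.

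**Step 2: put 120 in the numerator.** The denominator is n = 120 / rate.

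| Recruitment rate | x/n | Exact 95% CI | Half-width (points) |
|---|---|---|---|
| 50% (the plan's worst case) | 120/240 | 43.5% to 56.5% | 6.5 |
| 25% (Table 1 cut-off) | 120/480 | 21.2% to 29.1% | 4.0 |
| 10% (Table 1 cut-off) | 120/1200 | 8.4% to 11.8% | 1.7 |

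**Step 3: does the ±10% bound survive?** With 120 recruited and every eligible pool from 121 to 1300, the largest half-width is 7.1 points (at 120/178, or 67%). The exact interval is not symmetric, so the longer arm was checked too. Its largest value is 7.5 points (at 120/166, or 72%). Both are inside ±10.

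**Step 4: sensitivity to the stopping rule.** If recruitment simply stops at the 120th patient, the number recruited is fixed and the number of eligible patients is random. Exact limits under that sampling are 43.5% to 56.3% for 120/240, so the result hardly moves.

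**Step 5: the planned rate.** The number of eligible patients is not stated, so this step rests on assumptions.

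- Pool of 1300 × 10/12 = 1083 (assumes 1300 is a yearly figure cut to 10 months, which reproduces the stated 11%): 120/1083 = 11.1%, CI 9.3% to 13.1%, half-width 1.9.
- Pool of 1300 as printed: 120/1300 = 9.2%, CI 7.7% to 10.9%, half-width 1.6.

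The figure 1300 equals 1000 + 300, the two centres' yearly cardiac procedures. The trial takes only CABG patients who meet the other criteria, so the eligible number should be smaller and the rate among eligible patients higher than either figure.

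**The case against.** The strongest reply is that nothing operative is wrong. The claim is a bound, and the bound holds: at 50% the correct half-width is 6.5 points. The analysis text and Table 1 already use eligible patients, so the reported recruitment rate and its interval should come out right whatever the illustration says. Sample size, target, thresholds and go/no-go rule are untouched. All of this stands, and it is why the point is minor. It does not rescue the printed interval, which is attached to a rate it does not describe.

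Two stronger readings are tempting, and the article supports neither.

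- A reader might infer that the ±10% claim is false for recruitment, or that 120 patients are too few. Step 3 shows the opposite: precision is better than stated.
- A reader might infer that at the planned 11% the interval straddles the 10% stop line. Both intervals in step 5 do include 10%, but they rest on assumed pools of 1083 or 1300, apparently built from all cardiac procedures. Table 1 tests eligible patients, whose number is not given. It is also written in observed percentages, not confidence limits.

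Nor did the article undertake to show precision at each cut-off; it chose a 50% worst case. Giving the values at 10% and 25% makes the corrected sentence more useful, but their absence is not an error.

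**Conclusion.** The point holds as a correction of a stated figure. The 41% to 59% interval is valid for completion or drop-out among the 120 randomised patients and is not an interval for the recruitment rate. At the plan's own 50% the right interval is 43.5% to 56.5%, so the half-width is overstated by 9.3 − 6.5 = 2.8 points. The direction is conservative, the ±10% statement stays true, and 120 patients need not change. Severity is low.

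This rests on 120 actually being recruited and on the eligible-patient denominator in Data analysis and Table 1. One approximation remains: Table 1 counts patients who consent, and Randomisation and allocation allows for patients who consent but are not randomised and do not count towards the 120. The Table 1 numerator may therefore slightly exceed 120.

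Keeping 60/120 for drop-out needs a caveat. Table 1 judges completion in intervention patients only, so the denominator for that criterion is 60. At 50% its interval is 37% to 63%, about ±13 points, the same as the article already gives for adherence. The ±10% applies to completion across both arms, not to that criterion.

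**What to change.** In Sample size, take recruitment out of the 60/120 example and replace it with wording such as:

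> 120 recruited patients estimate a recruitment rate of 50% (120/240) with exact 95% CI 43.5%–56.5%, 25% (120/480) with 21.2%–29.1%, and 10% (120/1200) with 8.4%–11.8%.

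Keep 60/120 (41%–59%) for completion or drop-out across both arms only, and add that the Table 1 completion criterion rests on the 60 intervention patients (37%–63% at 50%).

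If an interval at the planned rate is wanted, label it an assumption and give the range: 9.3%–13.1% for 120/1083 (1300 × 10/12) and 7.7%–10.9% for 120/1300. Better still, state the expected number of eligible patients.

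The cost is two or three sentences. No extra patients are needed, and the analysis and progression criteria do not change.

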### Study procedure overview

Each participant will be involved for 2 months (baseline to 60-day follow-up). Patients will be enrolled on the study and randomised after surgery but prior to discharge or up until day five after surgery, whichever comes first. Patients in the control group will have standard postoperative wound care follow-up. Patients in the intervention group will receive digital surgical wound monitoring with the AI module for 30 days after surgery and also standard postoperative wound care follow-up. 30 days after surgery, all patients will be invited to complete an online survey, and a subsample of ten participants from each group will be interviewed. All patients will be phoned at 30 days and 60 days. The participant’s journey through the study is shown in the flow diagram in figure 1. Participants are free to withdraw at any time without providing a reason and without affecting their ongoing care. Additionally, staff will be invited to complete an online survey after 30 days and a subsample of 10 staff will be interviewed.

**Figure 1 F1:**
[figure not shown]
WISDOM Study flow diagram. AI, artificial intelligence; CABG, coronary artery bypass graft; WISDOM, Wound Imaging Software Digital platfOrM.

### Recruitment and consent

Initial screening by a member of the usual care team will take place before surgery with final eligibility for study enrolment assessed after surgery.

Potential participants will be identified by the usual care team through screening surgical admissions lists and will be given brief information about the study at admission and when they are in the postoperative ward after surgery. If they express an interest in taking part, they will be provided with a leaflet and an opportunity to discuss the study and ask questions. This will be done by an appropriately delegated member of the team. The information will make it clear that the decision for whether they are allocated digital monitoring with the AI module, or not, will be random.

For patients admitted preoperatively, information will be provided preoperatively giving a minimum of 24 hours between receiving information about the study and seeking consent. For patients transferred in on the day of surgery, information will be given postoperatively with a minimum of 24 hours before consent is sought.

Informed consent will be obtained before any trial activities commence including data collection. Participants will be asked at enrolment how they wish to receive dissemination information about the study (text/email/post). Participants who complete data collection will be offered financial recompense for their time. We will not recruit patients who are unable to give consent.

As the interviews will be remote, consent for patients participating in the substudy will be conducted remotely. The researcher will cover the information leaflet and consent form with the participant on the recording, but only the researcher will sign the consent form. The participant giving consent will be audio recorded and transcribed.

Participants are free to decline involvement in the study without giving a reason, although where reasons are given, these will be collected as part of screening data. If patients do not wish to participate, they will continue to receive standard postoperative care and their standard of care will not change.

